### Informed consent procedure

Informed assent (as appropriate) and consent will be obtained from children
and/or parents/guardians following explanation and understanding of the study
aims, objectives and processes. A member of the clinical team will first
approach the parent(s)/guardian(s) of the child. If interested, they will be
introduced to a research team member who will explain the study aims,
procedures, and urine sampling methods. Families will be provided with a
parent/guardian information leaflet and an explainer video; children will
receive age-appropriate information sheets. Time will be given (approximately
one hour) to consider participation and ask questions.

Written consent to join Part 1 of the study, including randomisation, will then
be sought. Families who decline randomisation will receive standard care and be
registered in the study system. Parents/guardians and children (over 5 years)
consenting and non-consenting to randomisation in Part 1 remain eligible for
Parts 2 and 3 of the study.

### Trial interventions

Eligible participants who consent to be randomised will be assigned to one of the
interventions; Invasive Trans-Urethral Bladder Catheterisation (TUBC) or
Invasive Suprapubic Aspiration (SPA) or Non-invasive Clean Catch Urine (CCU) (
Figure 3).

TUBC involves passing a flexible catheter into the bladder via the urethra. SPA
involves placing a needle through the skin of the abdomen directly into the
bladder. Non-invasive urine collection involves catching a urine sample in a
small dish. Sites will follow local policies and procedures for urine sampling
collection. In the event that a sampling method has been discontinued, an
alternative and clinically appropriate sampling method will be administered to
the child. Adherence to intervention and comparator will be recorded by
discontinuation of sampling method. These procedures are not protocolised and
will be performed, discontinued or modified in accordance with standard local
practice. Sampling method will be discontinued at the patient’s request
and guided by clinical judgement. Post-trial care will be provided as per
standard local clinical practice. A full summary of all trial interventions is
shown in Figure 5.

**Figure 5. f5:**
[figure not shown]
Visual summary of invasive urine sampling methods; Suprapubic
Aspiration (SPA) and Transurethral Bladder Catheterisation
(TUBC).

### Assignment of intervention

Participants will be recruited and randomised via an automated web-based system
using randomly permuted blocks in a 1:1:1 ratio to CCU, TUBC, or SPA. If one of
the invasive methods is contraindicated or unavailable, it will be excluded, and
randomisation will proceed between the remaining options. Participants can be
included as long as one invasive method is appropriate and available. In such
cases, randomisation will occur in a 1:1 ratio between CCU and the available
invasive method.

The randomisation sequence will be managed by a third-party provider and
concealed from the trial statistician and those enrolling participants.
Allocation will remain concealed until the point of randomisation. Blinding will
not be applied thereafter, reflecting the pragmatic design focused on assessing
feasibility for a future trial.

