### Secondary outcomes

1. Age, gender, ethnicity and basic demographic data of participants who
consent

2. Proportion of presenting patients who are judged unsuitable for the study

3. Proportion of participants with consent for randomisation to CCU, TUBC or
SPA

4. Proportion of participants with consent for randomisation to CCU or TUBC
only

5. Proportion of participants with consent for randomisation to CCU or SPA
only

6. Proportion of participants in each randomised group who received the allocated
intervention

7. Rates of contamination by urine collection method

8. Safety as defined as the incidence of adverse events

9. Time to collect urine sample

10. Pain score associated with urine sampling

11. Final diagnosis of UTI

12. Resource use and costs

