### Data management and monitoring

Participant data will be entered into screening and clinical databases and
processed in accordance with the Data Management Plan (DMP). Electronic data
queries will be issued to site staff to clarify or complete missing information,
with responses and amendments made directly within the study database.
Monitoring, audits, ethics reviews, and regulatory inspections will be conducted
with site agreement and access to source data and documentation. Patient safety,
adverse events and serious adverse events will be routinely monitored and
reported to the trial coordinating centre across host sites.

Confidentiality will be maintained in line with applicable laws and regulations.
Data validation checks will identify discrepancies such as out-of-range values,
inconsistencies, or protocol deviations. A Data Monitoring and Ethics Committee
(DMEC) will review study data at scheduled intervals. The study will adhere to
best practice principles for sharing individual participant data from publicly
funded clinical trials ^
32
^. Host sites, Sponsor and funder will be notified of substantial and
non-substantial study amendments through CPMS and the trial coordinating
centre.

### Data analysis part 1

As this is a feasibility study, analysis will be descriptive in nature. We will
describe baseline characteristics and outcomes using suitable measures of
central tendencies; means and medians with the associated standard
deviations/interquartile ranges for continuous data; and frequencies and
proportions for categorical data. A sensitivity analysis will be performed to
determine numbers of children perceived to be at higher risk, the reasoning as
to why they were higher risk (e.g. age, fever, signs of sepsis, symptoms) and
the proportion of higher and lower risk children successfully recruited and
randomised. Interim analysis will be conducted including safety reporting to the
independent DMEC, who provide input to final decisions made by the Trial
Steering Committee (TSC).

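### Children are randomised in three sets, depending on which invasive methods can be used, but contamination and adherence are grouped by method or arm without regard to set, so crude by-method figures, mainly those for SPA, are not like-for-like comparisons

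*Protocol article*

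**What the plan says.** All references are to the protocol article.

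- **Assignment of intervention.** Children are randomised "using randomly permuted blocks in a 1:1:1 ratio to CCU, TUBC, or SPA". When one of "the invasive methods is contraindicated or unavailable, it will be excluded, and" the draw is made among the remaining options: in such "cases, randomisation will occur in a 1:1 ratio between CCU and the available" invasive method. There are thus three sets: three-way (CCU/TUBC/SPA), CCU/TUBC only, and CCU/SPA only.
- **Secondary outcomes, items 3 to 5.** Consent is counted separately for the three sets; the first of these items reads "3. Proportion of participants with consent for randomisation to CCU, TUBC or" SPA. Set membership will therefore be known for every randomised child.
- **Secondary outcomes, items 6 and 7.** Adherence is grouped by randomised arm ("6. Proportion of participants in each randomised group who received the allocated" intervention) and contamination by method ("Rates of contamination by urine collection method"). Neither mentions the set. Adverse events, time to collection, pain and final diagnosis (items 8 to 11) carry no stated grouping.
- **Data analysis part 1.** The section opens "As this is a feasibility study, analysis will be descriptive in nature. We will" and goes on to list summary measures. It does not mention the set.
- **Trial interventions.** If a method is discontinued, another may be used, so the method received can differ from the method allocated.
- **Part 3 Consensus meeting.** Stakeholders consider the study's data and, if a trial is judged feasible, agree on TUBC, SPA or both for the invasive side.

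**The concern.** A child in the three-way set has a 1/3 chance of CCU. A child in a two-way set has a 1/2 chance of CCU and no chance of the method that was ruled out. Entry to a set depends on the child (contraindication) and on the setting (availability), and either may be related to contamination, collection time or pain.

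The groups formed by allocated method then differ in make-up by design. A crude table with one column per method would set SPA children, all of whom were suitable for SPA, beside CCU and TUBC children, some of whom were not. Part of any difference would reflect who could be offered SPA rather than what SPA does.

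That table is what a Part 3 attendee would naturally consult when choosing between TUBC and SPA. TUBC against SPA is a randomised contrast only within the three-way set.

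**Working it through.** The article gives no figure to reproduce: there is no power calculation, and it gives neither set shares nor set-specific rates. What follows is expected-value arithmetic on assumed inputs.

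**Inputs.** From the article: N = 100 and allocation ratios of 1:1:1, 1:1 and 1:1. Assumed: the number of children in each set (a three-way, t CCU/TUBC, s CCU/SPA) and an outcome rate for each set. No method effect is allowed within any set, so any difference between pooled groups comes from mixing sets.

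**Expected group sizes.**
- CCU = a/3 + t/2 + s/2
- TUBC = a/3 + t/2
- SPA = a/3 + s/2

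**Pooled differences.** CCU has the same make-up as SPA plus the t/2 children from the CCU/TUBC set, and the same make-up as TUBC plus the s/2 children from the CCU/SPA set. Hence:
- CCU − SPA = (t/2)/CCU × (rate in CCU/TUBC set − pooled SPA rate)
- CCU − TUBC = (s/2)/CCU × (rate in CCU/SPA set − pooled TUBC rate)

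**Simple example.** Take a = 60, t = 40, s = 0, with rates of 10% in the three-way set and 30% in the CCU/TUBC set.
- CCU = 60/3 + 40/2 = 40; TUBC = 40; SPA = 20.
- CCU and TUBC: (20 × 0.10 + 20 × 0.30)/40 = 20%.
- SPA: 10%, half the other two with no method effect.
- TUBC and SPA combined: (8 + 2)/60 = 16.7%, against 20% for CCU.

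**Range of set shares.** Rates are assumed at 30% in the CCU/TUBC set and 15% in the other two. Differences are in percentage points, from unrounded rates.

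| a/t/s | CCU, TUBC, SPA (n) | Pooled rates (%) | CCU − TUBC | CCU − SPA | TUBC − SPA |
|---|---|---|---|---|---|
| 100/0/0 | 33.3, 33.3, 33.3 | 15.0, 15.0, 15.0 | 0.0 | 0.0 | 0.0 |
| 80/15/5 | 36.7, 34.2, 29.2 | 18.1, 18.3, 15.0 | −0.2 | 3.1 | 3.3 |
| 60/30/10 | 40.0, 35.0, 25.0 | 20.6, 21.4, 15.0 | −0.8 | 5.6 | 6.4 |
| 40/50/10 | 43.3, 38.3, 18.3 | 23.7, 24.8, 15.0 | −1.1 | 8.7 | 9.8 |
| 20/70/10 | 46.7, 41.7, 11.7 | 26.2, 27.6, 15.0 | −1.4 | 11.3 | 12.6 |
| 34/33/33 | 44.3, 27.8, 27.8 | 20.6, 23.9, 15.0 | −3.3 | 5.6 | 8.9 |

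The 40/50/10 row in full: CCU = (13.33 × 0.15 + 25 × 0.30 + 5 × 0.15)/43.33 = 10.25/43.33 = 23.7%; TUBC = (2 + 7.5)/38.33 = 24.8%; SPA = 15%.

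**Range of rates.**
- 30% against 25% elsewhere: CCU − SPA is 1.0 to 3.7 points across the mixed-set rows.
- 40% against 20% elsewhere: at 20/70/10, CCU − SPA is 15.0 and TUBC − SPA 16.8; at 34/33/33, CCU − TUBC reaches −4.4, the largest value found for that contrast.
- Equal rates: every difference is 0.

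**Scale.** The Background cites contamination of 12% for TUBC and 1% for SPA, a gap of 11 points. The artefact in the 40/50/10 row (9.8 points) is close to that.

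**Restricted contrasts.** If TUBC is compared with CCU only in the three-way and CCU/TUBC sets, and SPA with CCU only in the three-way and CCU/SPA sets, the spurious difference is 0.0 in every row, because the two methods are allocated equally within each set used. In the 40/50/10 row, TUBC and the matching CCU children are both (2 + 7.5)/38.33 = 24.8%. TUBC against SPA in the three-way set has 40/3 ≈ 13 per arm if 40 children are in that set, and 33 if all 100 are.

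**The case against.** Three stronger readings are tempting, and the article supports none of them.

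- *The randomisation is lost.* It is not. It holds within each set, and the restricted contrasts recover it.
- *The plan commits to pooling outcomes across sets.* The article never says so. It attaches a grouping only to items 6 and 7, and silence on the set is not a commitment to ignore it.
- *A combined invasive group will be compared with CCU.* No such analysis is stated. The 16.7% against 20% above shows only what would happen if someone made that comparison without stratifying.

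The best defence goes further. The Part 1 analysis is descriptive, and no test or effect estimate between arms is stated. The primary outcome is a consent proportion, and the only numerical progression criterion, 33% recruitment, compares no arms. Adherence and adverse-event counts by method are useful even if the groups are not exchangeable. A statistical analysis plan exists but is not shown and may already split tables by set. The sizes rest on assumed shares and rates. Splitting every table would give seven arm-by-set cells, about 14 children each on average, and a CCU/SPA set of 10 would give about 5 per arm.

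Most of this stands, and it limits the point. It does not remove it. The make-up of the groups follows from the allocation rule without any assumption; only the size of the effect needs one. A descriptive table carries the same distortion as a test would. The grouping by method is what the article itself states, and the Part 3 choice between TUBC and SPA draws on the contrasts most exposed.

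**Conclusion.** The point holds as a matter of how by-method figures are presented and read. Contamination tabulated by collection method across the three sets is not a like-for-like randomised comparison, and the same applies to time, pain and UTI diagnosis if they are tabulated that way.

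The effect falls mainly on SPA against CCU and SPA against TUBC. Under the assumed inputs it runs from 0 (all children in the three-way set, or equal rates across sets) to about 10 points or more where many children are in the CCU/TUBC set and that set's rate differs by 15 points. The direction would reverse if that set had the lower rate. CCU against TUBC moves little when few children are in the CCU/SPA set (−0.2 to −1.4 points in the table) and by −4.4 at most in the scenarios run. All of these scenarios give the CCU/SPA set the same rate as the three-way set.

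The primary outcome, the recruitment criterion and the validity of randomisation within sets are not in question.

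**What to change.** State in the protocol or the analysis plan that:

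- the randomisation set is used as a stratum wherever methods are set side by side on contamination, time, pain or UTI diagnosis;
- TUBC is compared with CCU only in the three-way and CCU/TUBC sets, SPA with CCU only in the three-way and CCU/SPA sets, and TUBC with SPA only in the three-way set;
- any comparison of invasive methods together against CCU is stratified by set, because the invasive share is 2/3 in the three-way set and 1/2 in the others;
- these summaries group children by allocated method, and results by method received are shown separately;
- overall by-method totals for adherence and adverse events are kept, labelled as non-comparative.

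No new data are needed, since the randomisation and the consent outcomes already require the set to be known. The cost is a few extra table columns and smaller cells, most of all for TUBC against SPA, where the restricted contrast may have few children per arm.

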### Participant assessments

The frequency of assessments and patient journey are detailed in Figure 4 and Figure 6.

**Figure 6. f6:**
[figure not shown]
SPIRIT ^
26, 27
^ Schedule of enrolment, interventions and assessments.

### Data collection

Each participant will be allocated their own unique participant study number
during the recruitment/randomisation process, which will be used throughout the
study for participant identification on all data collection forms and
questionnaires. An entry will be recorded in the patients’ medical notes
noting enrolment into the study.

All data for an individual participant will be collected and recorded in source
documents and transferred onto a bespoke, web-based, electronic case report form
(eCRF) for the study. For routinely collected clinical data, the NHS record will
be the source document. The Modular Resource-Use Measure ^
28
^ will be administered between 3–6 months post urine sampling
method. SUDS ^
29
^ distress and pain scores (Wong Baker ^
30
^, FLACC ^
31
^ will be child and parent reported respectively following administration
of urine sampling. Participant identification on the eCRF will be through their
unique participant study number, allocated at the time of randomisation. Adverse
event (AE) reporting will follow the Health Research Authority (HRA) guidelines
on safety reporting in non-CTIMP studies. Available outcome data will be
collected for participants who discontinue or deviate from the protocol.

### Data management and monitoring

Participant data will be entered into screening and clinical databases and
processed in accordance with the Data Management Plan (DMP). Electronic data
queries will be issued to site staff to clarify or complete missing information,
with responses and amendments made directly within the study database.
Monitoring, audits, ethics reviews, and regulatory inspections will be conducted
with site agreement and access to source data and documentation. Patient safety,
adverse events and serious adverse events will be routinely monitored and
reported to the trial coordinating centre across host sites.

Confidentiality will be maintained in line with applicable laws and regulations.
Data validation checks will identify discrepancies such as out-of-range values,
inconsistencies, or protocol deviations. A Data Monitoring and Ethics Committee
(DMEC) will review study data at scheduled intervals. The study will adhere to
best practice principles for sharing individual participant data from publicly
funded clinical trials ^
32
^. Host sites, Sponsor and funder will be notified of substantial and
non-substantial study amendments through CPMS and the trial coordinating
centre.

### Data analysis part 1

As this is a feasibility study, analysis will be descriptive in nature. We will
describe baseline characteristics and outcomes using suitable measures of
central tendencies; means and medians with the associated standard
deviations/interquartile ranges for continuous data; and frequencies and
proportions for categorical data. A sensitivity analysis will be performed to
determine numbers of children perceived to be at higher risk, the reasoning as
to why they were higher risk (e.g. age, fever, signs of sepsis, symptoms) and
the proportion of higher and lower risk children successfully recruited and
randomised. Interim analysis will be conducted including safety reporting to the
independent DMEC, who provide input to final decisions made by the Trial
Steering Committee (TSC).

### Health economics analysis

A detailed costing analysis will be performed of the different methods of urine
collection in children up to the point of achieving a definitive sample from a
hospital perspective. Resource use will be prospectively collected as will staff
time (nursing and medical) and equipment for each method in a sub sample of
episodes from each site. A version of the ModRUM ^
28
^ adapted for completion by a parent/guardian will be used to collect
healthcare resource use after the participants have left the hospital setting up
to a maximum of 6 months post-randomisation. Unit costs from publicly available
sources (e.g. NHS Reference Costs, unit costs of health and social care) will be
applied to the resource use where possible. Other sources, such as hospital
costing departments and the literature, will be used when this is not possible.
Costs will be presented in GBP£. Costs associated with the initial
sampling will be included as will any repeat sampling and any follow up
investigations to estimate the mean cost per definitive UTI diagnosis ^
33
^. Sensitivity analyses will be performed to explore impact on the cost
estimates of variations in key parameters e.g. time estimates, staff grade.

## Part 2: Mixed methods perspectives study

An embedded mixed methods study will explore the perspectives of parents, children,
young people, and healthcare practitioners about the feasibility of the proposed
trial. This research will include a perspectives’ questionnaire which will be
set within the randomised feasibility trial (Part 1). Interviews will be conducted
with parents and children as well as focus groups and interviews with HCPs who are
involved in and conducted the randomised feasibility trial (Part 1). Participants
external to the feasibility trial will also be sought from social media channels
enabling sample diversity. An exploration of topics will provide qualitative and
quantitative insight into the acceptability of different sampling collection
methods, the population for inclusion in a future study, potential barriers to
recruitment and consent and important patient centred outcomes for use in a future
trial.

### Part 2 Population: Parents/ guardians and children

*Inclusion criteria*

Parents/guardians of children (0 to under 16 years) and children (aged 7 to under
16 years) who are approached to participate in Part 1, including those who
decline randomisation are eligible to take part in Part 2 of the study.

In addition, parents/guardians of children (0 to under 16 years) and children
(aged 7 to under 16 years) who have required urine testing in hospital setting
for suspected UTI in the last three years are also eligible to take part in the
perspectives’ aspect of feasibility.

*Exclusion Criteria* for part 2 of the study include
language issues (not overcome with use of translators and available translated
information sheets) and those who declined consent to join Part 2.

### Part 2 Method: Interviews and questionnaires with parents/guardians and
children

**
*Recruitment and sampling*
**

**Recruitment Route 1: Hospital Sites hosting the randomised controlled
feasibility trial**

Participants, including those that decline randomisation, recruited during Part 1
will be invited to the perspectives’ study element (Part 2) and asked to
complete a brief perspectives questionnaire following the study recruitment
discussion. If both parents are present, both will be asked to consent and
complete a questionnaire. Based on previous studies in similar settings, 50
completed questionnaires are expected.

Parents will also be invited to take part in an interview with a researcher from
the University of Liverpool at a later date. Child assent and parental consent
will also be sought for children to take part in an individual or joint
interview with parents if the child is deemed well enough to broach the study at
that point in time.

**Recruitment Route 2: Social Media**

To ensure diversity across geographic regions and ethnicities within the UK,
participants will be recruited through tailored social media advertising and
targeted emails to relevant UK-based charities and organisations. The research
team will contact gatekeepers (e.g. charity leads/Chief Executive Officers) of
support groups for parents/legal representatives whose children have required
urine testing for suspected UTI in the last three years. The research team will
send an age and language-appropriate Participant Information Sheet, check
eligibility and whether a translator will be required for the interview.
Potential participants will be asked to read the study information and ask any
questions they may have before being sent a link by email to an online consent
form to complete. An email or paper version can be sent on request if preferred
(e.g. for children). Purposeful sampling will be conducted to ensure parents and
children (aged 7 to under 16 years) reflect the various settings, ethnic
diversity and representation of age ranges of infants, children and young people
who would be eligible for a definitive study ^
34– 36
^.

